Research undertaken as a pilot study for this project examined the impact of the South West Ambulance Service NHS Foundation Trust’s (SWAST) CCT on survival from OHCA [21]. This retrospective database analysis compared survival to hospital discharge between 165 cases of OHCA attended by CCTs and 1686 cases attended by ALS-paramedics. While survival was significantly higher in the CCT group than the ALS-paramedic group (15.8% and 6.5%, respectively, *p* < 0.001), this was largely due to an imbalance in prognostic factors. After adjusting for these, using multiple logistic regression, there was no significant benefit from CCT attendance in this sample (OR 1.54, 95% CI 0.89–2.67, *p* = 0.13).

Currently, all EMS in the UK dispatch paramedics trained in advanced life support (ALS) to confirmed or suspected OHCA [3]. Prehospital critical care teams (CCTs) are utilised by some but not all NHS ambulance trusts, and their availability varies significantly across regions [9, 22]. This results in large variations in the care and resources available for OHCA, possibly reflecting the uncertainty regarding the clinical benefits of CCTs [9, 23].

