## Methods

All included NHS ambulance trusts dispatch prehospital critical care teams to confirmed or suspected OHCA. While the CCTs will aim to attend most cases of OHCA, they will inevitably be unavailable for a proportion of these, due to already having been dispatched to another case of critical illness or injury, or the limitations imposed by operational duty hours and constrained funding. This results in a natural experiment where one group of patients is attended by the CCT and another is treated by ALS-trained paramedics. By comparing rates of survival to hospital discharge between these two groups, we will be able to measure the impact of prehospital critical care.

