### Research sites

Study recruitment will take place in up to four NHS ambulance trusts. This combination will cover both rural and urban areas of the UK. All four ambulance trusts dispatch CCTs to OHCA by helicopter or in a rapid response vehicle, depending on time of day, weather and geographical considerations. We have shown in our previous research that prehospital critical care competencies are few in number, and of these few, only a fraction apply to prehospital critical care for OHCA [10]. We therefore anticipate that the team composition, critical care competencies and relevant protocols vary only slightly between the CCTs of the different trusts. These slight differences will not influence the results to any important degree regarding the impact of prehospital critical care (as a concept) on survival. We will compare CCT protocols prior to data collection, and the individual critical care interventions delivered for each case of OHCA will be recorded.

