### Data collection

We will analyse consecutive cases of adult OHCA, according to the inclusion and exclusion criteria. The study is planned to commence in September 2016 and continue for 18 months or until 6000 cases have been included, whichever occurs first.

Data collection will be from two data sources.

Ambulance trusts in the UK collect OHCA data routinely for quality assurance, independently of this research. These data are based largely on the Utstein variables and are recorded in regional databases. Participating ambulance trusts will provide data from their databases to the researchers. This first data source includes the following variables required for this research project:▪ Medical identifying number▪ Date and time▪ Location (public place, private location or nursing home)▪ Postcode of event (district level)▪ Age-group and gender of patient▪ Do Not Attempt Resuscitation order in place▪ EMS chest compressions▪ Witnessed event▪ Bystander CPR▪ Public access defibrillator used by bystander▪ Suspected cause▪ First EMS resource response time▪ First recorded cardiac rhythm▪ ROSC on arrival at hospital▪ Receiving hospital (if transported to hospital)▪ Survival to hospital discharge

In addition, we will collect data from the critical care teams (CCTs). Most CCTs keep a local electronic database of all cases where the CCT was requested, including the broad category of event (for example trauma, OHCA, medical). We will integrate a few additional data requests for every case identified as OHCA, specifically for this research:▪ Medical identifying number▪ Stand down prior to arrival at patient▪ CCT requested by ALS ambulance crew on scene▪ CCT members: Critical care paramedic and/or doctor▪ CCT response time▪ Interventions delivered during cardiac arrest▪ Interventions delivered after return of spontaneous circulation (ROSC)▪ Transport decisions and modalities▪ Provider decision to not provide full critical care in patient’s best interest

If no electronic CCT database exists, the required data will be collected on a simple paper form for each CCT OHCA case. The ambulance trust database and CCT data from each participating ambulance trust will be merged using the medical identifying number, creating the CCT and ALs groups.

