Propensity score matching will involve the following steps [29]:We will run a logistic regression with CCT attendance as the dependent variable. Prognostic factors for both survival to hospital discharge and CCT dispatch will be covariates. They will include age and gender of the patient, the cause and location of OHCA, whether it was witnessed, bystander CPR, ambulance response time, first recorded rhythm and distance from CCT base. This will allow us to calculate a propensity score for each patient - the probability of the patient receiving CCT treatment.We will then match each CCT case with ALS-trained paramedic cases of OHCA, with similar propensity scores. This will be done using nearest neighbour matching within a specified calliper distance - the ‘greedy algorithm’ assigns controls with similar propensity scores to each case. To qualify as 'matching' the propensity score of potential controls needs to be within 0.2 of the pooled standard deviation of the logit of the propensity score [30]. This reduces the risk of bias from matching controls to cases whose propensity scores differ too much. To optimise available data, we will match each CCT case with up to five ALS-paramedic controls whose propensity scores are within the defined caliper, accepting varying numbers of controls per case. Each control will only be available for matching once and then will be removed from the control pool [31].We will compare the matched CCT and ALS-paramedic groups to verify that prognostic factors are balanced between the groups.We will analyse for statistically significant differences in survival to hospital discharge between the groups (see also ‘3.2.5 data analysis’).

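### The propensity covariates that are named leave out ambulance trust, and matching is on the score alone, so CCT cases can be matched to ALS controls from other trusts.

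*Protocol article*

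**What the plan says.** The propensity-score steps (Data analysis) give a rule, "Prognostic factors for both survival to hospital discharge and CCT dispatch will be covariates", and then a list: "They will include age and gender of the patient, the cause and location of OHCA, whether it was witnessed, bystander CPR, ambulance response time", followed by "first recorded rhythm and distance from CCT base". That makes nine variables. Each CCT case is then matched to up to five ALS controls by nearest neighbour within a caliper on the logit of the score. No exact matching or stratification is described. The next step checks that prognostic factors are balanced between the matched groups. The primary outcome is analysed by conditional logistic regression in the matched groups and by multivariable logistic regression in the full cohort. No covariates are listed for the full-cohort model.

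Other sections bear on this list:

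- **Research sites:** "Study recruitment will take place in up to four NHS ambulance trusts", covering rural and urban areas.
- **Background (Prehospital critical care for OHCA):** on CCTs in the UK, "their availability varies significantly across regions".
- **Methods, opening paragraph:** among the reasons a CCT may be unavailable, "the limitations imposed by operational duty hours and constrained funding".
- **Data collection:** date and time are collected, as is "Public access defibrillator used by bystander". Trust is not a listed variable, but it is known from the source, because "The ambulance trust database and CCT data from each participating ambulance trust will be merged using the medical identifying number". Location is recorded as type of place, not as region.

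**The concern.** The study pools patients over several ambulance trusts, whereas the pilot examined one service's CCT. Pooling brings in a possible confounder that the pilot did not face. Trusts can differ in how often a CCT attends and in survival for reasons other than the CCT, such as ALS performance and receiving hospitals. The protocol gives grounds to expect the second: its Background links reported survival of 5% to 38% to differences in prehospital treatment, and its Discussion raises hospital treatment as a possible confounder.

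If trusts with more CCT attendance also have better underlying survival, CCT care looks better than it is. If they have worse survival, it looks less good. The result is meant to guide commissioning, so a modest bias in the odds ratio matters even if it would rarely decide significance.

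Two lesser gaps follow from the same list. Time of day is collected and is tied to CCT availability, and public-access defibrillation is collected and belongs to a class of treatment that the Background calls consistently beneficial. Neither is named as a covariate.

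**Working it through.** **1. Do the named variables capture trust?** The nine are age, gender, cause, location, witnessed status, bystander CPR, ambulance response time, first rhythm and distance from CCT base. Location means public place, private location or nursing home. Distance from base can be the same in two trusts. Response time may carry part of a trust difference but does not identify the trust. So two patients with equal scores may come from different trusts.

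**2. How large could the bias be?** The plan gives no trust-level rates, so the inputs here are assumptions: two trusts A and B of equal size, no CCT effect, attendance a and survival s in each, and none of the difference explained by the nine covariates.

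- CCT survival = (a_A·s_A + a_B·s_B) / (a_A + a_B)
- ALS survival = [(1−a_A)·s_A + (1−a_B)·s_B] / (2 − a_A − a_B)

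| Attendance A, B | Survival A, B | CCT | ALS | Difference | OR |
|---|---|---|---|---|---|
| 15%, 5% | 9%, 6% | 0.0165/0.20 = 8.25% | 0.1335/1.80 = 7.42% | +0.8 points | 1.12 |
| 15%, 5% | 10%, 5% | 0.0175/0.20 = 8.75% | 0.1325/1.80 = 7.36% | +1.4 points | 1.21 |
| 12%, 8% | 9%, 6% | 0.0156/0.20 = 7.80% | 0.1344/1.80 = 7.47% | +0.3 points | 1.05 |
| 12%, 8% | 10%, 5% | 0.0160/0.20 = 8.00% | 0.1340/1.80 = 7.44% | +0.6 points | 1.08 |

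Mean attendance (10%) and mean survival (7.5%) agree with the Data analysis and Sample size sections. Reversing the survival rates reverses the sign.

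**3. Against what yardstick?** With 600 CCT cases and 1200 controls at 7.5%, the standard error of the difference is √[0.075 × 0.925 × (1/600 + 1/1200)] = 1.3 points. The plan states a detectable difference of about 4.5 points. (A two-sided pooled formula gives 4.05; nothing here depends on which is used.) The illustrated bias is well below either figure, and only the largest case exceeds one standard error. Against the pilot's adjusted odds ratio of 1.54, it is ln 1.12 / ln 1.54 = 0.113/0.432 = 26%, up to ln 1.21 / ln 1.54 = 0.191/0.432 = 44%, of the log odds ratio in the strong-contrast rows.

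**4. What does matching on the score do?** A small simulation used assumed effects: 6000 patients, four equal trusts, 60% of arrests by day, attendance depending on trust and time, two controls per case and 40 replicates. With trust and time left out of the score, about 76% of matched pairs mixed trusts. Daytime arrests were 85% of CCT cases but 56% of controls. With both in the score, daytime was 85% v 84%, and 61% to 62% of pairs still mixed trusts. Adding a variable to the score thus balances it on average without preventing mixed sets. With so few replicates, the simulation is not used to size the bias.

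**5. Time of day.** Suppose 90% of CCT cases and 60% of matched controls fall in CCT duty hours, with controls at 7.5% survival. The spurious difference is (0.90 − 0.60) × (survival on duty − survival off duty). If duty hours carried a survival odds ratio of 1.2, 1.5 or 2.0, it would be 0.4, 0.8 or 1.3 points. If they carried 1.0, it would be zero. The documents do not say which applies.

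**The case against.** The strongest reply is that the covariate list is open. It follows a sound rule and is introduced as what the covariates will include, in an article that condenses a fuller plan. That stands: a reader might infer that trust is excluded, and the text does not say so. Likewise, the balance check is on prognostic factors in general, so it cannot be said that the check would necessarily miss trust. What remains is that the rule is followed by a specific list and that nothing in the article adds trust.

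A reader might also infer that the plan itself says region drives attendance in this study. The regional statement describes the UK as a whole, where some trusts have no CCT. All participating trusts dispatch CCTs, so variation between them is plausible but not stated. Distance from base may absorb part of it.

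It is tempting to call time of day a confounder. Duty hours are given as a cause of CCT absence, but no section says that time affects survival. If it affects availability only, leaving it out causes no bias, and adjusting for it costs overlap, since off-duty periods have almost no CCT cases.

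For public-access defibrillation, nothing says that it influences dispatch, and first rhythm, bystander CPR and location partly stand in for it.

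Finally, the trust illustration uses crude rates. The nine covariates will explain part of any difference, so only what is left counts. This is accepted.

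The assurance under Research sites that differences between trusts are slight does not answer the point. It concerns CCT composition, competencies and protocols, not ALS performance, hospitals or CCT coverage.

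**Conclusion.** The point holds for trust: it should be fixed, with moderate confidence. Trust is absent from the named covariates, nothing else named identifies it, and matching is on the score alone. The bias requires residual trust differences in both attendance and survival. Its illustrated size is an odds ratio of about 1.1 to 1.2 under a strong attendance contrast, and 1.05 to 1.08 under a mild one, on assumed rates before the listed covariates act. That would colour the estimate more than it would decide significance.

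Time of day and defibrillator use are secondary. The documents support time as a driver of availability and early defibrillation as prognostic. They do not support either as a demonstrated confounder, nor the conclusion that the primary comparison is invalid without them.

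**What to change.** **Main change.** Match exactly within trust, or at the least put trust in the propensity score. Include trust in the full-cohort regression, and report balance by trust after matching. Putting trust in the score addresses average imbalance; exact matching also guarantees that no set mixes trusts. Trust is fixed before the CCT acts, so it is a safer adjustment than receiving hospital, which the plan says CCT care may itself change.

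**Secondary additions.** Add public-access defibrillator use to the score and the outcome model. Report balance on a time-of-day band, with a sensitivity analysis that adjusts for it or is restricted to hours when a CCT operates.

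**Cost.** Date, time and defibrillator use are already collected, and trust follows from the data source. Exact matching loses some controls, but the pool is large: 5400/600 = 9 ALS cases per CCT case overall, and 0.85/0.15 = 5.7 in a trust with 15% attendance, before the caliper is applied. The sample size assumes two. Adjusting for time may reduce overlap, which is why it belongs in a sensitivity analysis. CCT operating hours are not among the listed variables and would have to be obtained from each trust.

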### Aims and objectives

This prospective, observational study will describe the effect of CCTs on survival from OHCA, when compared to advanced-life-support (ALS), the current standard of prehospital care in the UK. In addition, we will describe the association between individual critical care interventions and survival. A stakeholder-focused cost analysis will describe the costs of CCTs for OHCA, in relation to public donations to charity and EMS commissioning.

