The matching process will result in two groups of OHCA patients: an intervention group that has been attended by a CCT in addition to the usual ambulance response, and a control group that has been attended by ALS-trained paramedics alone. We will compare the primary outcome of survival to hospital discharge between OHCA attended by the CCT and OHCA attended by ALS-trained paramedics. We will conduct multivariable logistic regression analyses for the full cohort and conditional logistic regression for the propensity score matched groups. We will also undertake subgroup analysis for witnessed OHCA with shockable rhythm, with the hypothesis that any potential benefit of CCT attendance will be more pronounced. There is a possibility that any observed benefit from CCT care is due partially to CCTs conveying more patients to a cardiac centre, bypassing nearer hospitals. We will therefore also compare the secondary outcome of survival to hospital admission.

In addition, we will describe the frequency of prehospital critical care interventions delivered by the CCTs for OHCA. We will then undertake logistic regression analysis including known predictors of survival, with the individual critical care interventions as independent variables and survival to hospital discharge as a dependent variable. We estimate that there will be enough survivors of OHCA to allow multiple logistic regression with up to ten variables (estimated 100 survivors, with 10 outcomes per variable). However, should this not be possible, we will describe frequency of critical care interventions occurring during OHCA treatment, which will be useful information when interpreting the overall results of this project.

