### Sample size

Data for the South Western Ambulance Service from our pilot study shows that resuscitation for OHCA was commenced by prehospital providers in approximately 100 cases during the month. Rates of survival average 7.5%. We estimate that after application of inclusion and exclusion criteria, we will be able to include 6000 patients, of which approximately 600 will be CCT cases. This will allow us to detect an absolute improvement in survival rates of approximately 4.5% with a power of 0.8 and alpha 0.05, assuming one-to-two matching and a survival rate of 7.5% in the control group.

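### The planned regression of survival on individual critical care interventions does not separate post-ROSC from in-arrest items, so a post-ROSC item with no effect would tend to look protective

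*Protocol article*

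**What the plan says.** The Aims and objectives section of the protocol article states that "we will describe the association between individual critical care interventions and survival". The Data analysis section gives the method, to follow a description of frequencies. The covariates are covered by the phrase "logistic regression analysis including known predictors of survival". The exposures and the outcome are then set by a model "with the individual critical care interventions as independent variables and survival to hospital discharge as a dependent variable". Its size is justified by an "estimated 100 survivors, with 10 outcomes per variable", which gives up to ten variables. If that is not achievable, frequencies alone will be reported.

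The Data collection section asks the CCTs for two separate items: "Interventions delivered during cardiac arrest" and "Interventions delivered after return of spontaneous circulation (ROSC". The routine ambulance data contribute "ROSC on arrival at hospital". No section splits the regression by timing, limits the post-ROSC items to patients with ROSC, states which patients enter the model, or lists the predictors to be adjusted for.

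**The concern.** An intervention given after ROSC can reach only patients who achieved ROSC, and survival to discharge all but requires ROSC. If patients who never had ROSC are in the model, they all count as untreated and nearly all die. The coefficient of a post-ROSC item then largely measures whether ROSC occurred. Adjustment for factors fixed before treatment, such as rhythm or witnessed status, does not remove this.

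In-arrest items face a different problem. Longer, more refractory arrests leave more time to accumulate interventions, which may make these items look harmful.

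At stake is a stated secondary aim: the intervention-level odds ratios could reflect when an intervention can be given, not any relation between the intervention and survival.

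**Working it through.** **The plan's own figure.** 100 survivors / 10 outcomes per variable = 10 variables, as stated. The 100 survivors fits the CCT group: the Sample size section expects 6000 patients, "of which approximately 600 will be CCT cases", and the pilot's CCT survival was 15.8% (Background), so 600 x 0.158 = 94.8. The full cohort at the average survival of 7.5% would give 6000 x 0.075 = 450. The figure therefore points to CCT cases. It cannot tell all CCT cases from CCT cases with ROSC, because nearly every survivor has ROSC.

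**Spurious odds ratio, closed form.** Let r be the proportion with ROSC, s overall survival, and g the share of ROSC patients given the intervention. Assume that every survivor had ROSC, that the intervention is given at random among ROSC patients, and that it has no effect.

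- Survival if treated = s / r
- Survival if untreated = s(1 - g) / (1 - g r)

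Survival of 15.8% is the pilot CCT figure, and 12% is the design figure (7.5% + 4.5%). The values of r and g, and the lower survival value of 9.5%, are assumptions; the documents give none of them.

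- Central case, r = 0.40, s = 0.12, g = 0.50: treated 0.12 / 0.40 = 0.30; untreated 0.06 / 0.80 = 0.075; OR = (0.30/0.70) / (0.075/0.925) = 5.29.
- Low end, r = 0.50, s = 0.095, g = 0.30: treated 0.19; untreated 0.0665 / 0.85 = 0.0782; OR = 2.76.
- High end, r = 0.30, s = 0.158, g = 0.70: treated 0.527; untreated 0.0474 / 0.79 = 0.060; OR = 17.4.

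**With covariate adjustment.** A simulation used 600 cases, 15.8% survival, no true effect, adjustment for one prognostic score, and 300 runs per scenario:

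| ROSC | Use among ROSC patients | Crude OR, closed form | Median adjusted OR, all cases | Runs with p < 0.05, all cases | Median adjusted OR, ROSC only |
|---|---|---|---|---|---|
| 30% | 30% | 8.04 | 6.15 | 99.7% | 0.99 |
| 30% | 70% | 17.43 | 12.09 | 100% | 0.98 |
| 40% | 30% | 4.54 | 3.33 | 96.3% | 1.00 |
| 40% | 70% | 9.26 | 6.29 | 100% | 1.01 |
| 50% | 30% | 3.09 | 2.28 | 77.0% | 0.98 |
| 50% | 70% | 5.87 | 4.01 | 100% | 0.98 |

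With use as low as 10%, the adjusted OR at 50% ROSC was 2.05 and 38.7% of runs were falsely significant. Over all scenarios, restriction to ROSC patients gave ORs of 0.97-1.02 and rejection rates of 1.7-7.7%, against a nominal 5%.

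**How much selective use would cancel it.** Take r = 0.40, s = 0.158, g = 0.30. For the overall OR to equal 1, treated survival must be 0.158. Survival in untreated ROSC patients is then (0.158 - 0.12 x 0.158) / 0.28 = 0.497. The within-ROSC OR would be (0.158/0.842) / (0.497/0.503) = 0.19. Concentration in the sickest patients would reduce the bias, but cancelling it would take very strong selection.

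**The case against.** A reader might infer that the plan enters all interventions in one model over all CCT cases with baseline covariates only, that any post-ROSC item must then look strongly protective, and that funding decisions will follow. The documents do not support this reading, for these reasons:

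- **Analysis set.** It is not stated, and the survivor count does not settle it. The article describes one regression but does not say in terms that both kinds of item enter it together. Recording them separately is compatible with a split analysis. Leaving the analysis set to a fuller document is ordinary and is no fault in itself.
- **Covariates.** The predictors are not listed. The list of prognostic factors in the article belongs to the propensity model. ROSC at hospital arrival is collected and might be intended as a covariate.
- **Size.** ROSC and uptake rates are assumed and use is taken as random. A rarely used item, or one reserved for the sickest, could show less bias or miss significance. The bias in the in-arrest items has no figure at all.
- **Use.** The Discussion's remark on guiding practice and funding refers mainly to the overall effects, the costs and the description of interventions. The regression is framed as association throughout.

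These points limit the claim without removing it. Adjusting one pooled model for ROSC would largely repair the post-ROSC items but would adjust away part of any in-arrest effect. Restricting one pooled model to ROSC patients would condition on the result that in-arrest items are meant to bring about. No single model handles both kinds of item, whichever way the gaps are filled.

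**Conclusion.** The concern holds conditionally. If the regression is fitted to CCT cases without separating interventions by timing, a post-ROSC item with no effect will tend to look protective. The crude OR is about 2.8 to 17 under ROSC of 30-50%, survival of 9.5-15.8% and random use in 30-70% of ROSC patients, and smaller with selective use in the sickest. An opposite bias in the in-arrest items is plausible but unquantified.

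The point deserves correction before analysis but is not critical to the study. It concerns a secondary aim worded as association and backed by a descriptive fallback. The primary CCT-versus-ALS comparison is unaffected.

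**What to change.** Replace the single regression with two models and state the analysis set of each:

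1. **Post-ROSC interventions:** only CCT cases with ROSC.
2. **In-arrest interventions:** a separate model without adjustment for ROSC, excluding patients already in ROSC when the CCT arrived, where this is known.

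Report both as associations, not effects.

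**Cost.** This is more than a change of wording. With the variables now listed, ROSC at hospital arrival is the available proxy for the first set. It is imperfect, because it misses patients who had ROSC, were treated and re-arrested before hospital. Defining the sets properly needs one or two tick-box items (in arrest at CCT arrival; any ROSC), added to the CCT data request that the study is already extending. Each model will have fewer patients and may support fewer variables. If either becomes too small, the frequency description already planned is the fallback.

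### As worded, the intervention regression does not confine post-ROSC interventions to patients who had ROSC, so an inert one would look beneficial unless ROSC is handled

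*Protocol article*

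**What the plan says.** Under Aims and objectives, the protocol article states that "we will describe the association between individual critical care interventions and survival". Under Data collection, the CCT data request has two separate intervention fields: "Interventions delivered during cardiac arrest" and "Interventions delivered after return of spontaneous circulation (ROSC"). The ambulance trust database supplies "ROSC on arrival at hospital".

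Under Data analysis, the model is described in one sentence. Its covariates are given only in general terms ("We will then undertake logistic regression analysis including known predictors of survival"), and that sentence goes on to define the exposures and the outcome: "with the individual critical care interventions as independent variables and survival to hospital discharge as a dependent variable". The size of the model is justified by "estimated 100 survivors, with 10 outcomes per variable", which allows up to ten variables. If that proves impossible, the authors will describe frequencies only.

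The sentence does not split the interventions by phase, state an analysis population or list the known predictors. The only prognostic factors the article does list belong to the propensity score: age, gender, cause and location, followed by "whether it was witnessed, bystander CPR, ambulance response time, first recorded rhythm and distance from CCT base". ROSC is not among them.

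**The concern.** A post-ROSC intervention can, by definition, be given only to a patient who has regained circulation. If the model covers CCT cases with and without ROSC, the untreated group for such an item contains every patient who died without ROSC. Having received the item then marks that the patient passed the main gate to survival, whatever the item itself does. Baseline factors such as age, rhythm and witnessed status predict ROSC only partly, so adjusting for them leaves most of the distortion in place.

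At stake is the post-ROSC half of a stated objective. Large and significant associations would be reported for post-ROSC care whether or not it works, and readers could not tell a real association from one created by who was able to be treated.

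**Working it through.** **The plan's own figure.** 100 survivors / 10 outcomes per variable = 10 variables, as stated. The 100 is consistent with the whole CCT group: 600 CCT cases (Sample size) x 15.8% CCT survival in the pilot (Background) = 94.8. It is not consistent with the full cohort, where 6000 x 7.5% = 450. It cannot separate all CCT cases from CCT cases with ROSC, because nearly all survivors are in both.

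**Inputs.** From the article: 600 CCT cases and 100 survivors, so overall survival S = 100/600 = 16.7%. Assumed, because the article gives no figure: ROSC share r = 30-60%; share of ROSC patients given the item q = 30-70%, at random; survival without ROSC 0-1%. The item has no effect, so the true odds ratio (OR) is 1.

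**Closed form, no survival without ROSC.**
- Survival if given: S / r
- Survival if not given: S(1 - q) / (1 - rq)

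With r = 40% and q = 50%, 240 of the 600 have ROSC and 120 of these are treated.
- Given: 50 of 120 survive (41.7%).
- Not given: 50 of 480 survive (10.4%), the 480 being 120 with ROSC and 360 without.
- OR = (50/70) / (50/430) = 6.14.
- ROSC patients only: 50/120 against 50/120, OR = 1.

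With the pilot's 15.8% in place of 16.7%: 0.158/0.40 = 39.5% against 0.079/0.80 = 9.9%, OR 5.96.

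Over the whole grid the crude OR runs from 2.32 to 18.50 with no survival without ROSC, and from 2.22 to 15.23 with 1% survival without ROSC.

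**Simulation with baseline adjustment.** 300 data sets per row, 600 cases each, survival without ROSC 0.5%, logistic regression on the item plus three baseline factors (shockable rhythm, witnessed status, one continuous factor) that predict both ROSC and survival. OR is the median; the percentage is the share of data sets with p < 0.05.

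| ROSC | Treated among ROSC | All CCT cases: OR | p < 0.05 | ROSC patients only: OR | p < 0.05 |
|---|---|---|---|---|---|
| 30% | 30% | 7.59 | 100% | 1.00 | 4.7% |
| 30% | 70% | 16.74 | 100% | 0.99 | 6.3% |
| 40% | 50% | 5.81 | 100% | 1.00 | 4.3% |
| 50% | 30% | 2.82 | 95.7% | 1.01 | 4.7% |
| 50% | 70% | 5.38 | 100% | 0.99 | 7.3% |
| 60% | 30% | 2.17 | 82.0% | 1.03 | 6.3% |
| 60% | 70% | 3.57 | 100% | 1.01 | 6.0% |

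Over all twelve combinations run, the OR in all CCT cases was 2.17 to 16.74. In ROSC patients only it was 0.96 to 1.03, significant in 4.0-7.3%. Adding ROSC as a covariate gave 0.97 to 1.05, significant in 3.6-8.3%, although 5 to 35 of the 300 fits failed in each combination.

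**Several items at once.** With three inert post-ROSC items in one model, the OR for an item was 3.17 (94% significant) at ROSC 40% and 30% treated, and 2.34 (85%) at ROSC 50% and 50% treated. Sharing the model dilutes the bias but does not remove it.

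**The case against.** The strongest reply is that the criticised model is partly inferred. A reader might take the article to say outright that one regression is fitted over all CCT patients. It does not: neither the population nor the number of models is stated. The known predictors are also left open, and if they included ROSC the calculation above shows that most of the bias would go. Covariate lists for a secondary model are often left to the analysis plan. The data fields would also allow an analysis by phase.

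This makes the finding conditional but does not dispose of it. The model is stated, its variables are the individual interventions, these include post-ROSC items, and nothing in the text confines those items to patients who could receive them. The fallback to frequencies is tied to too few survivors and not to this problem. A single ROSC covariate is also not a clean repair. The recorded status is at hospital arrival, which misses patients who were treated after ROSC and re-arrested. ROSC also lies downstream of in-arrest interventions, so adjusting for it in a shared model would distort their associations.

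A second reply is that only associations are claimed. That softens the interpretation but does not correct the estimate.

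Two wider inferences are tempting and are not supported:
- *Transport items suffer the same bias in this model.* Transport decisions are a field separate from the interventions, and the model sentence does not enter them.
- *The Discussion says this regression will guide practice and funding.* It attaches that use to the effects and costs of CCTs together with a description of the interventions, not to the regression.

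**Conclusion.** The point holds in conditional form. On the plain reading of Data analysis, and unless ROSC is handled, an inert post-ROSC intervention would show an adjusted OR of about 2 to 17 where the true value is 1, and would be significant in 82-100% of simulated studies. The size depends on the assumed ROSC rates (30-60%) and treatment frequencies (30-70%), which the article does not give. The direction was the same at every combination tried.

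A reader might conclude that the whole intervention objective, or the study's main result, is compromised. The documents do not support that. In-arrest interventions are outside this mechanism, and the primary CCT against advanced life support comparison does not use this model.

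**What to change.** In Data analysis, state two models:
1. Post-ROSC interventions, analysed only in CCT patients with ROSC at any time during CCT attendance.
2. In-arrest interventions, analysed separately in patients in arrest during CCT attendance.

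If this cannot be done, report frequencies only for post-ROSC items.

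Add two yes/no items to the CCT data request: arrest status at CCT arrival, and ROSC at any time during attendance. Neither is listed under Data collection, and status at hospital arrival cannot fully reconstruct them, so they should be in place before collection starts.

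The cost is a change of wording and two short form items. The post-ROSC model loses almost no survivors, so its variable budget is hardly touched. The in-arrest model may lose survivors who had ROSC before the CCT arrived, and so may support fewer than ten variables; the article gives no figure from which to size this. Restriction removes the distortion from who could be treated. It does not remove confounding by indication among ROSC patients, and the report should say so.
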